#### Sample size and power

Enrollment of 96 subjects with 12% attrition at 3 months will give us 80% power to detect a .85 effect size between exergame and attention control.

### Variables and their measures

#### Primary and secondary outcomes

The primary outcome (Table 2) for this RCT is episodic memory, while secondary outcomes include executive function, global cognition, and aerobic fitness. Outcomes will be assessed at baseline and at 3 months by data collectors who are blinded to group allocation and previously collected data. All cognitive outcomes will be assessed through the NIH Toolbox Cognitive Battery (NIHTB-CB) [38, 39] according to NIH Toolbox Assessment Center instructions [39]. The NIHTB-CB, an interactive personal application device (iPAD) based battery of executive function, attention, episodic memory, language, processing speed, and working memory tests, was developed within the NIH Blueprint for Neuroscience Research and has been validated and normed in a broad sample of the US population [38, 39]. This battery yields summary scores such as the Cognitive Functioning Composite Score, in addition to individual measure scores as outlined below [38, 39].

**Table 2 Tab2:** Data collected from participants during the study

Variables	Measures (data type)	Data collection type	Screening period	Baseline/follow-up period
Cognitive outcomes				
Episodic memory	Picture Sequence Memory Test, Auditory Verbal Learning Test (both continuous)	NIH toolbox (iPAD)		x
Executive function	Cognitive Battery Flanker Inhibitory Control, Attention Test and Dimensional Change Card Sort Test (both continuous)	NIH toolbox (iPAD)		x
Global cognition	Composite score from all tests for discrete cognitive domains	NIH toolbox (iPAD)		x
Aerobic fitness outcomes				
Aerobic fitness	SWT (continuous)	Performance-based test		x
Other variables				
Depression	GDS (continuous)		x	
Anxiety	(Gas-10), BAI (both continuous)		x	
Physical function	SPPB, 6MWT (both continuous)	Performance-based test		x
Medical change	Medical diagnoses, falls, medications (all categorical)		Monthly	
Demographics	Age, education (both continuous) sex, race (both discrete)	Self-report, paper form	x	
Physical activity	Accelerometry, PASE questionnaire (both continuous)	Wrist device, pencil-paper-based questionnaire	Monthly	
Intervention adherence	Percent (continuous)	REDcap report		
Usability, acceptability, and satisfaction of exergame	Likert scale (ordinal)	Pencil-paper-based questionnaire	Monthly	

6MWT 6-min walk test, BAI Beck’s Anxiety Inventory, Gas-10 Geriatric Anxiety Scale – 10 item, GDS Geriatric Depression Scale, PASE Physical Activity Scale for the Elderly, SWT shuttle walk test

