**Methods/design:**

The purpose of this single-blinded, 3-parallel group randomized controlled trial is to test the synergistic efficacy of an exergame intervention (simultaneous moderate-intensity aerobic cycling and cognitive training) on cognition and aerobic fitness in community-dwelling older adults with SCD. The Exergames Study will randomize 96 participants on a 2:1:1 allocation ratio to 3-month exergame, cycling only, or attention control (stretching). Primary outcomes include global cognition and aerobic fitness, which will be assessed at baseline and after 3 months. The specific aims of the Exergames Study are to (1) determine the efficacy of the exergame in older adults with SCD and (2) assess the distraction effect of exergame on aerobic fitness. Data will be analyzed using ANOVA following intention-to-treat.

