### Study aims

The purpose of this phase II RCT is to test the efficacy and additive/synergistic effects of an exergames intervention (simultaneous moderate intensity cycling and cognitive training), in comparison to cycling only and attention control (stretching) on cognition and aerobic fitness in older adults with SCD. The specific aims and hypotheses of the study are described as follows:
Aim 1: Determine the efficacy of the exergame in older adults with SCD.Hypothesis: Exergame will improve global cognition more than cycling only and attention control.Aim 2: Assess the distraction effect of an exergame on aerobic fitness.Hypothesis 2a: Exergame participants will achieve similar gains in aerobic fitness to cycling participants.Hypothesis 2b. Exergame participants will achieve similar exercise intensity targets to cycling participants.

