Aim 1: Determine the efficacy of the exergame in older adults with SCD. To test our hypothesis that exergame will improve global cognition more than cycling only and attention control, the ANOVA will be performed. If statistically significant results are identified, then we will perform post hoc analysis to determine how the changes in cognition differ between groups. If homogeneity of variances are supported across the three groups, we will conduct Tukey’s honestly significant different post hoc test. If homogeneity of variances are violated, then we will perform the Games Howell post hoc test. If significant covariates are identified, then analysis of covariance (ANCOVA) will be used instead. Linear simple and multiple regressions will be performed to assess association between the effects of exergames on global cognition and aerobic fitness. A *p* value < 0.05 will be used to determine statistical significance. Effect size (EF) calculated as EF = (mean exergames group − mean stretching group)/SD (stretching group) will be used to assess the clinical significance of the effects of exergames on cognitive and aerobic fitness outcomes listed above.Aim 2: Assess the distraction effect of exergame on aerobic fitness. Our hypothesis that exergame participants will achieve similar gains in aerobic fitness to cycling participants will be analyzed similarly to aim 1 hypothesis using ANOVA and post hoc test. In addition, heart rate monitor data will be utilized to compute intensity dose, to compare objective effort given during exergame and cycling only sessions. We hypothesize that the average %HRR achieved by exergame participants will not be significantly different compared to cycling only participants. A standard formula will be used to quantify the intensity dose and is as follows. Percent HRR (%HRR) averaged in each session will be calculated from the following variables (EHR = exercise session average heart rate, PHR = peak heart rate from SWT, and RHR = resting heart rate from SWT) and formula: %HRR = [(EHR − RHR)]/(PHR − RHR)]. The %HRR will be averaged across all sessions to give a quantifiable index of intensity to be used as a surrogate measure of distraction. Differences between exergames and cycling only groups on average %HRR will be assessed by independent *T* test.

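### The Abstract and the Methods name different primary outcomes, and no stated hypothesis or test names the one in the Methods

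*Protocol article*

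**What the plan says.** All references are to the protocol article.

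- **Primary and secondary outcomes (Methods):** "The primary outcome (Table 2) for this RCT is episodic memory, while secondary outcomes include executive function, global cognition, and aerobic fitness".
- **Abstract, Methods/design:** "Primary outcomes include global cognition and aerobic fitness, which will be assessed at baseline and after 3 months".
- **Study aims, Aim 1 hypothesis:** "Exergame will improve global cognition more than cycling only and attention control". The Aim 2 hypotheses concern aerobic fitness (2a) and exercise intensity (2b).
- **Statistical analyses, Aim 1:** "To test our hypothesis that exergame will improve global cognition more than cycling only and attention control, the ANOVA will be performed". If the result is significant and variances are homogeneous, "we will conduct Tukey’s honestly significant different post hoc test"; otherwise Games-Howell is used.
- **Statistical analyses, Aim 2:** the aerobic fitness hypothesis "will be analyzed similarly to aim 1 hypothesis using ANOVA and post hoc test". A t test compares average heart-rate-reserve intensity between exergame and cycling.
- **Significance rule:** a p "value < 0.05 will be used to determine statistical significance", with no ranking of outcomes and no split of alpha among them.
- **Effect size:** a standardised exergame-versus-stretching difference "will be used to assess the clinical significance of the effects of exergames on cognitive and aerobic fitness outcomes listed above".
- **Sample size and power:** 96 participants with 12% attrition give 80% power for an effect size of .85 between exergame and attention control. No outcome is named.

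**The concern.** The primary outcome decides which test the trial is judged on, which outcome the sample size refers to, and which results are supportive. Here, global cognition and aerobic fitness are primary in one section and secondary in another. The outcome that the Methods call primary is absent from the Abstract's list of primaries and from every hypothesis. The contradiction lies between two statements in the same document, so it is not a matter of detail left to a fuller protocol or an analysis plan.

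Two things are at stake. Someone following the text exactly could not say which p value is the main result. And if a favourable result on either cognitive outcome could be reported as the primary success, the chance of a false claim exceeds the nominal 5%.

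**Working it through.** **1. The sections side by side**

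| Section | Episodic memory | Global cognition | Aerobic fitness |
|---|---|---|---|
| Abstract | not named | primary | primary |
| Primary and secondary outcomes | primary | secondary | secondary |
| Study aims | no hypothesis | Aim 1 | Aim 2 (2a) |
| Statistical analyses | not named | Aim 1 ANOVA | Aim 2 ANOVA |
| Sample size and power | no outcome named | no outcome named | no outcome named |

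Episodic memory can be reached in the analysis section only through general wording: model choice for each outcome, a post hoc step that speaks of cognition in general, and a descriptive effect size for cognitive outcomes.

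**2. Does the power statement identify the primary outcome?**

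Inputs: 48 exergame and 24 control (Design), 12% attrition and effect 0.85 (Sample size and power). Completers: 48 × 0.88 ≈ 42 and 24 × 0.88 ≈ 21; cycling also about 21.

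Noncentrality = 0.85 × √(42 × 21 / 63) = 0.85 × √14 = 3.18.

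- Tukey comparison among three groups (df = 84 − 3 = 81, critical value 2.388): power 78.4%; effect detectable with 80% power, 0.865.
- Two-sided t test at 0.025: 80.9%.
- Omnibus F test with cycling midway between the other groups: 81.7%.
- Unadjusted two-sided t test at 0.05: 87.9%.

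The stated 80% is therefore reproduced within about 2 points by a comparison adjusted for multiple groups, assuming two-sided testing. The effect is in standard-deviation units, so the figure fits any of the continuous outcomes equally well. It is not wrong, but it does not settle which outcome is primary.

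**3. What the ambiguity could cost in false positives**

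Assume each candidate is tested at 0.05, there is no true effect, and any one significant result could be presented as the primary success.

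*Two cognitive candidates (episodic memory, global cognition):*
- Independent: 1 − 0.95² = 9.8%.
- Correlated (simulated two-sided normal tests): 9.1% at r = 0.5, 8.3% at r = 0.7, 7.8% at r = 0.8.

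*Aerobic fitness added as a third candidate:*
- Independent: 1 − 0.95³ = 14.3%.
- Equal correlations of 0.3 to 0.8: 13.5% down to 9.9%.

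The document gives no correlations between outcomes, so these are assumptions shown as a range. Some correlation between the two cognitive candidates is expected, because the Global cognition section builds the composite partly from the episodic memory tests.

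**The case against.** The strongest opposing points concern how far the finding reaches.

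- **Three declared primaries.** A reader might infer that the plan names three rival primary outcomes. It makes two conflicting statements: a single primary in the Methods and a pair in the Abstract. Aim 1 does not use the word primary. This stands.
- **No rule between the two memory tests.** A reader might add that the Picture Sequence Memory Test and the RAVLT are unranked, which would make four candidates. The Episodic memory section already marks the RAVLT as supplementary; only Table 2 lists both without ranking. A four-candidate error rate is not supported.
- **Aerobic fitness as a third route to success.** Hypothesis 2a predicts similar gains with exergame and cycling, so a significant difference on that contrast counts against it. Only exergame versus stretching could give a positive claim, and no hypothesis states one. The two-candidate figures are therefore the fairer ones.
- **No analysis at all for episodic memory.** The general wording could cover it, descriptively at least. What holds is that no hypothesis or test names it.
- **Missing multiplicity control as a separate defect.** Tukey or Games-Howell handles the group pairs within each outcome. If the Methods statement governs, there is one primary and no alpha split is needed. The gap arises only from the conflicting labels.
- **A choice left open until the data are seen.** The registry record and any analysis plan are not at hand and might fix the primary. The article permits the ambiguity; it does not show that the choice is open. Nor does it point clearly to a resolving source, since Trial registration and Trial status give different registry identifiers.
- **Phase II purpose.** The trial is meant to supply effect sizes for later trials. That softens the matter, but the Abstract and the Study aims also say that it tests efficacy.

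None of this removes the conflict between the Abstract and the Methods.

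**Conclusion.** The point holds as an internal contradiction. The document gives two incompatible statements of the primary outcome, its named hypotheses and tests do not include the outcome that the Methods call primary, and the power statement does not break the tie. Followed as written, the main test is undefined.

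If either cognitive outcome could be reported as the primary success, the false-positive chance is 9.8% under independence and about 8-9% at assumed correlations of 0.5-0.8. The 14.3% is an upper bound that counts aerobic fitness as a third independent route. These figures describe what the ambiguity would allow. They are not evidence that outcomes will be selected after the fact, and the documents do not support that inference. The sample size is not called into question.

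**What to change.** Before any unblinded look at the data, state one primary outcome identically in the Abstract, Study aims, Sample size and power, Primary and secondary outcomes, and Statistical analyses, and label the others secondary. There are two workable routes:

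- **Global cognition:** name the NIH Toolbox Cognitive Functioning Composite. Aim 1 and its ANOVA already test it, so the least text changes.
- **Episodic memory:** name the Picture Sequence Memory Test as the single measure, align Table 2 with the supplementary status of the RAVLT, and rewrite the Aim 1 hypothesis and analysis to test it.

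If more than one primary is kept, state whether success is needed on all or on any, and give the multiplicity rule. As a guide, Bonferroni over three alternative primaries (alpha 0.05/3 = 0.0167, plain two-sided t test, 42 versus 21) gives about 76% power at 0.85, and the effect detectable with 80% power is about 0.89. This makes no further adjustment for the group comparisons.

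The cost is a documented amendment, ethics submission and registry update. Trial status reports enrolment as open since December 2019, so the amendment should be dated and justified as a mid-trial clarification or change of the primary outcome. No new data are needed. With a single primary and the planned Tukey comparison, power at 0.85 stays at about 78%, so N need not change. Up to two outcomes lose a primary label: under the first route these are episodic memory (from the Methods) and aerobic fitness (from the Abstract).

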#### Episodic memory

Episodic memory refers to cognitive processes involved in the acquisition, storage, and retrieval of new information and will be measured using the Picture Sequence Memory Test (PSMT) [39] and Auditory Verbal Learning Test (Rey) (RAVLT) [39] (supplementary measure). The PSMT has excellent test-retest reliability (*r* = 0.84) and is strongly correlated with the RAVLT, (*r* = .64), reflecting good convergent validity [40].

#### Executive function

Executive function refers to the capacity to plan, organize, and monitor the execution of goal-directed behaviors such as set-shifting and inhibitory control and will be measured by the Flanker Inhibitory Control and Attention Test [39] and Dimensional Change Card Sort Test [39]. Both tests demonstrate excellent sensitivity to age-related changes during adulthood, excellent test–retest reliability (*r* = .85), and adequate to good convergent validity (*r* = .52–.55) [41].

#### Global cognition

Global cognition refers to the overall cognitive ability and will be calculated as the NIHTB-CB Cognitive Functioning Composite Score (i.e., total score). The Cognitive Functioning Composite Score is calculated from the following domain-specific scores: language (Picture Vocabulary Test and Oral Reading Recognition Test), attention (Flanker Inhibitory Control and Attention Test), processing speed (Pattern Comparison Processing Speed Test and Oral Symbol Digit Test [supplementary measure]), and working memory (List Sorting Working Memory Test) in addition to the tests used to measure episodic memory and executive function. The composite score has high psychometric measurements including internal consistency (Cronbach’s alpha = .77), test-retest reliability (*r* = .90), and convergent validity (*r* = .89) in adults [42].

#### Aerobic fitness

Aerobic fitness will be assessed using the SWT, following the guidelines by Singh and colleagues [43]. Participants will be required to walk along a level, 10-m course at a previously determined speed dictated by signals from an audio recording. Laps will be counted for calculation of peak walking distance achieved during the SWT. The test will be considered finished when the participant is not able to maintain the required speed (more than 0.5 m from the cone) or for some other reported symptom that warrants test termination (i.e., American College of Sports Medicine [ACSM] clinical sign or symptom for exercise test termination) [33]. Because older adults with SCD may have trouble multitasking and remembering test instructions, we will provide additional instructions to ensure proper testing methodology including by providing additional verbal instruction including (1) “stop” when participants arrive at the marker before the beep, (2) “go” when the single beep for walking sounds, and (3) “go and walk faster now” when the triple beep sounds, indicating faster pace required [44]. The SWT reliability is well established in older adults with multiple chronic conditions (interclass correlation 0.91–.97) [45, 46]. Additionally, the peak walking distance on SWT is highly correlated to peak oxygen consumption derived from cardiopulmonary exercise testing in older adults with multiple chronic conditions [47], making it a valid test for assessing aerobic fitness.

### Study procedure

#### Study preparation and randomization

All staff will be adequately trained to ensure participant safety, blinding, data quality, and protocol adherence based on the Study Manual of Operations. Prior to any recruitment, the statistician will create a randomization schedule in Research Electronic Data Capture (REDCap). Qualified participants will be randomized after completing baseline data collection. The study coordinator will log into the REDCap randomization module and enter a participant’s name/age. The randomization module will assign the participant to a group and record the assignment in a database that is only accessible to unblinded staff.

#### Data collection

Enrolled subjects will be scheduled to complete baseline data collection. Subsequent data collection will occur at 3 months. Data collectors will be independent from study interventionists to help insure data integrity. To ensure the blindness of the data collectors from the intervention assignment, the data collectors will not interact with enrolled subjects except for data collection.

#### Delivery of the assigned activity for each group

Within 2 weeks of completing baseline data collection, participants will start their assigned activity: exergames, cycling only, or attention control. Each activity will consist of a total of three weekly, supervised sessions for 3 months (36 total sessions). One interventionist will supervise up to three participants in a single visit (1:3 interventionist/participant ratio) in the same activity. The sessions will be delivered over up to a 14-week period to account for missing sessions due to vacations and illnesses.

#### Cycling group

Subjects will cycle on recumbent stationary cycles at moderate intensity individualized as 50–70% of heart rate reserve (HRR) and/or 11–14 on Borg Category Ratio-15 Rating of Perceived Exertion (RPE) Scale. HRR will be calculated by subtracting resting HR (after 10-min quiet resting) from the peak HR achieved during the SWT. Cycling will be progressed from 50–60% of HRR or RPE 11–12 for 30–35 min in session 1 and will be alternatively increased by 5% of HRR (or 1-point on Borg) or 5-min increments as tolerated up to 60–70% of HRR (or RPE 12–14) for 50 min a session over time. All sessions will include a 5-min warm-up and 5 cool-down before and after cycling, in addition to the prescribed exercise duration, following the ACSM guidelines [33]. In each session, the interventionists will help subjects put on a Polar™ wireless HR monitor (RS400, Lake Success, NY), take resting HR and blood pressure, and monitor HR, RPE, talk test, and signs and symptoms every 5 min, and blood pressure every 15 min.

#### Exergame

Subjects will cycle as described in the cycling protocol while engaging in cognitive training for the duration of cycling. Cognitive training will include one level of difficulty with six task scenarios in the context of three virtual worlds (environments): “Small-Town Downtown,” “Underwater World,” and “Wild West.” For example, the virtual world of “Small-Town Downtown” will be composed of shops, restaurants, storefronts, and office buildings. Each environment will be open-world and static and will not change over time or between game sessions. This will allow the participant to memorize the layout over multiple play sessions. Visual cues (“Landmarks”) will serve as memorization guides for navigation. Landmark examples for “Small-Town Downtown” include unique buildings, bridges, statues, parks, and other true-to-the-environment objects. Scenarios will have high ecological validity. Scenario examples in “Small-Town Downtown” include (1) picking up and dropping off a delivery for a friend, (2) visiting the post office to mail a letter, (3) sorting books at the library, and (4) going shopping at the grocery store. In each of the environments, the participant must follow directions and navigate to a destination where the cognitive task will be performed. For each scenario, participant start position within the environment will be randomly assigned by the system. A scenario-specific cognitive task will be triggered. The game will inform the participant of the assigned task and, automatically, determine and inform the participant of the fastest route from the starting point to the scenario destination where the task will be performed. The participant will be required to remember the assigned task, follow the directions and navigate to the destination, and then remember what action is required to complete the task. The participant will move forward through the environment by pedaling the stationary cycle. Left and right turns along the route will be input by the participant through buttons on the game controller. To enable a smooth transition into the cognitive task while maintaining cycling movement, the game’s camera will continue to progress in a forward direction to match participant pedaling speed, while the level environment fades into a desaturated surreal version of each scenario’s setting.

